#### Secondary outcomes

##### GP behaviour

The secondary outcomes include measures of GPs’ diagnostic behaviours (Table 2). The chosen behaviours are recommendations from the SIGN guideline [3], including some adaptation for the Australian context (*e*.*g*., referral to CDAMS, details of adaptation available in Table 1). Two behaviours, ‘review of medications’ and ‘ordering of pathology tests’ are not recommendations of the SIGN guideline, but were considered best practice by the IRIS clinical investigators (Table 1). We have also included outcomes (dementia diagnosis, reported suspicion of cognitive impairment) measuring whether the intervention is effective in raising GPs’ awareness and diagnosis of cognitive impairment and dementia for all patients aged 70 years and older (cohort 1).

##### Proxy measures of GP behaviour

Proxy measures of all GP diagnostic behaviours have been included. For some diagnostic behaviours (referral to specialist, review of medications, ordering of pathology tests), it is not possible to use the CAT. Proxy measures provide an alternative method for measuring behaviour in such circumstances, and there is some evidence showing they are predictive of behaviour [43]. We have included proxy measures for the two management behaviours, disclosure of diagnosis of dementia to (i) patients and (ii) carers. While disclosure of diagnosis is not a recommendation of the SIGN guideline, there are many ethical arguments favouring disclosure [44], and the IRIS clinical investigators strongly advocated for disclosure. Furthermore, disclosure was identified as salient in the interviews with GPs in phase I of this project.

##### Mediators of GP behaviour

For the two key recommendations (undertaking a formal assessment for cognitive impairment and for depression), potential mediators of GP behaviour include measures of behavioural constructs (*e*.*g*., emotion, knowledge, skills, and social influences) (Table 3). These mediators reflect the barriers and enablers that were identified in phase I of this project (through interviews with GPs), and were targeted through the intervention components. We include measures of intention to adhere to the two key recommendations, since intention in many theories is considered the most immediate predictor of behaviour [45], and we hypothesise that intention will mediate the relationship between GPs’ motivation and behaviour. If the intervention is effective, we posit that differences in these mediators between groups will be observed. Figure 2 displays the causal pathway demonstrating the hypothesised relationship between the intervention, mediators and behaviour. Examination of the effects of the intervention along the causal pathway has been restricted to the primary outcomes to limit respondent burden.

**Table 3 T3:** Behavioural construct domains (hypothesised mediators of GP behaviour)

**Domains**	**Domain definitions **[27]** (adapted from Michie *****et al*****. **[40]**)**	**Domain measured for behaviour**	
		Cognitive assessment^1^	Depression assessment^2^
*Motivation*			
Intention^3^	A conscious decision to perform a behaviour or a resolve to act in a certain way	✓	✓
Beliefs about capabilities	Acceptance of the truth, reality or validity about an ability, talent or facility that a person can put to constructive use	✓	✓
Beliefs about consequences	Acceptance of the truth, reality or validity about outcomes of a behaviour in a given situation	✓	✓
Emotion	A complex reaction pattern, involving experiential, behavioural and physiological elements, by which the individual attempts to deal with a personally significant matter or event	✓	✓
*Capability*			
Knowledge	An awareness of the existence of something	✓	✓
Skills	An ability or proficiency acquired through practice	✓	✓
Memory, attention and decision processes	The ability to retain information, focus selectively on aspects of the environment, and choose between two or more alternatives	✗	✓
*Opportunity*			
Environmental context and resources	Any circumstance of a person’s situation or environment that discourages or encourages the development of skills and abilities, independence, social competence, and adaptive behaviour	✓	✓
Social influences	Those interpersonal processes that can cause individuals to change their thoughts, feelings or behaviours	✓	✗

^1^Cognitive assessment using MMSE. Three items per behavioural construct domain, except for Beliefs about consequences, which is four items; providing a total of 25 items.

^2^Depression assessment using validated scale. Three items per behavioural construct domain, except for Beliefs about consequences, which is four items; providing a total of 25 items.

^3^Intention referred to as ‘Motivation and goals’ in the Theoretical Domains Framework [40].

**Figure 2 F2:**
[figure not shown]
Hypothesised causal pathway model for the primary outcomes.

We have included measures of intention for the two management behaviours, disclosure of diagnosis of dementia to (i) patients and (ii) carers.

### Outcome measurement

Table 4 provides a summary of the measurement tools. In brief, GPs’ detection and diagnostic behaviours will be measured through the CAT where possible. Proxy measures and mediators of GP behaviour will be measured through a paper-based questionnaire (available in Additional file 1 - IRIS behavioural construct questionnaire).

**Table 4 T4:** Summary of measurement tools

**Outcome or category of outcomes**	**Measurement tool**	**Details**
*GP behaviour*		
Cognitive assessment using MMSE	CAT electronic search^†^	MMSE results recorded in the patient file or free text indicates an MMSE has been undertaken.
Depression assessment using validated scale	CAT electronic search^†^	Geriatric Depression Scale (GDS) results recorded in the patient file or free text indicates GDS, Hamilton Rating Scale for Depression, Even Briefer Assessment Scale for Depression has been undertaken.
Referral to CDAMS or specialist	CAT electronic search^†^	Free text indicates that the patient has been referred to CDAMS, ACAS (Aged Care Assessment Service), or a geriatrician.
Referral for CT scan	CAT electronic search^†^	CT scan has been requested or free text indicates that a CT (head) scan has been requested/undertaken.
Dementia diagnosis	CAT electronic search^†^	Coded diagnosis of dementia or free text indicates that the patient has dementia or Alzheimer’s disease.
Cognitive assessment using MMSE (all patients aged 70+ years)	CAT electronic search^†^	MMSE results recorded in the patient file or free text indicates an MMSE has been undertaken.
Reported suspicion of cognitive impairment (all patients aged 70+ years)	CAT electronic search^†^	Coded diagnosis of cognitive impairment or free text indicates a suspicion of cognitive impairment (*e*.*g*., confusion, muddled, cognitive), or; MMSE undertaken in isolation of the 75+ Health Check (an indication of GP’s suspicion of cognitive impairment), or; MMSE undertaken as part of 75+ Health Check with score indicating cognitive impairment (*i*.*e*., a score between 10 and 24).
Dementia diagnosis (all patients aged 70+ years)	CAT electronic search^†^	Coded diagnosis of dementia or free text indicates that the patient has dementia or Alzheimer’s disease.
*Proxy measures of GP behaviour*		
Self-report of adherence to recommended behaviours (*e*.*g*., Cognitive assessment using MMSE)	Questionnaire* (1 item per behaviour)	Adapted from Eccles *et al*. [45]. Example item: ‘Thinking about the last 10 patients you saw who you suspected had cognitive impairment, how many of them did you assess for cognitive function using the Mini Mental State Examination (MMSE)?’
Behavioural simulation to adhere to recommended behaviours (e.g., Cognitive assessment using MMSE)	Questionnaire (6 clinical vignettes)	Vignettes simulate clinical decision-making about detection, diagnosis and management of dementia. Vignettes include a range of clinical variables: sex, age (72 – 88 years), cognitive function (including changes to memory, personality, behaviour, cognition), depression, and other elements. These clinical variables were drawn from previously published vignettes [46-52] and from the experience of the clinical investigators. The vignettes, and response options, will be piloted with two to three GPs prior to being administered.
*Hypothesised mediators of GP behaviour*		
Intention to adhere to recommended behaviours (*e*.*g*., Cognitive assessment using MMSE)	Questionnaire* (3 items per behaviour)	Adapted from Eccles *et al*. [45], Francis *et al*. [53],and Foy *et al*. [54]. Items for Cognitive assessment using MMSE include ‘I would make it a high priority to use the MMSE to assess the cognitive function of these patients,’ ‘I plan to use the MMSE to assess the cognitive function of these patients,’ ‘I intend to use the MMSE to assess the cognitive function of these patients.’ Each item measured on a 7-point Likert scale ranging from strongly disagree to strongly agree (1 to 7). Scores are then averaged to create a behavioural intention score. Higher scores reflect greater intention to assess cognitive function using the MMSE.
Behavioural constructs for primary outcomes	Questionnaire*	Adapted from [34]. There are 49 items in total. Example of the items used to measure various domains (noted in brackets) for the behaviour depression assessment using a validated scale include: ‘How much do you know about validated scales for assessing depression in these patients?’ (knowledge), ‘Using a validated scale to assess these patients for depression is sometimes stressful’ (emotion), ‘Lack of time may prevent me from using a validated scale to assess these patients for depression’ (environmental context and resources). Each item is measured on a 7-point Likert scale. All constructs are measured using three items (which are averaged to create a final score for the construct), except beliefs about consequences, which is measured using four items.

^*^Questionnaire available in Additional file 1 – IRIS Behavioural construct questionnaire. ^†^ Two researchers (with healthcare qualifications), who are blind to intervention group, will independently review the free text entries to decide if the behaviour has occurred. Disagreements will be resolved via discussion with a geriatrician who will not be informed of the group allocation of the patient.

### Data quality assurance

GP questionnaires will be checked for errors and missing data as they are returned, and GPs will be followed up to clarify anomalies. Double data entry will be used to enter GP paper-based questionnaires. Inconsistencies will be investigated by referring back to the paper-based version. Non-responding GPs will be contacted by phone to encourage completion of the questionnaire.

Free text entries extracted from the CAT contain a maximum of 40 characters surrounding the identified search term, to maintain anonymity of the patients. The short length of these text extracts is likely to lead to difficulties in coding variables for some patients. Therefore, two researchers, who are blind to intervention group, will independently review the text extracts. To improve consistency in coding between researchers, a coding dictionary will initially be created from a sample of text extracts. Disagreements will be resolved via discussion with a geriatrician who will not be informed of the group allocation of the patient.

### Sample size

The primary outcomes of the IRIS trial include cognitive assessment using MMSE and depression assessment using a validated scale in patients with suspected cognitive impairment (cohort 2). The trial has been powered to detect a difference of 15% in rates of the behaviours between groups (assuming control group rates of 50%). Using sample size formula (2) of Eldridge *et al*. [55] and assuming, on average 20 patients per practice are identified, with a coefficient of variation in practice size of 0.7, and an intra-cluster correlation of 0.10, 45 practices per group will be sufficient to detect the 15% increase in recommended behaviours with 90% power (two-sided significance level of 5%). Allowing for 25% attrition in practices, we aim to recruit 60 practices per group. Justifications of the parameters used in the sample size calculation are available in Additional file 2 – IRIS sample size calculations.

### Effectiveness analyses

#### Analysis subsets

Intention-to-treat (ITT) analyses are generally recommended in randomised trials for the primary reason of preserving the benefits of randomisation; namely, maintaining the comparability of the intervention groups in known and unknown prognostic factors [56]. In addition, it has been argued that ITT analyses compared with other analysis strategies (*e*.*g*., per-protocol) are more appropriate for pragmatic trials since they provide estimates of intervention effect that are more reflective of what would be observed if the intervention was implemented in routine clinical practice [57-59].

While requirements of an ideal ITT analysis (including compliance with the randomised intervention, no missing responses, and follow-up on all participants [57]) have been established for patient randomised trials, only recently has there been more detailed discussion of the definition and application of ITT analyses in C-RTs [60]. In C-RTs with adequate allocation concealment, comparability of intervention groups can be compromised not only through missing responses and loss to follow-up (as occurs in patient randomised trials), but also through recruitment of participants occurring post randomisation. Furthermore, loss to follow-up in cluster trials can occur at different levels (clusters and patients) because of the hierarchical structure of the design.

In the IRIS trial, retrospective identification of eligible participants will be undertaken (post randomisation) by researchers blind to group allocation, so the potential for selection bias will be minimised. In addition, bias arising from missing responses and loss to follow-up at the patient level will be minimal, since data will be extracted through the CAT on all eligible patients. However, practices and GPs may withdraw prior to data being extracted on their patients, resulting in empty clusters. A full application of the ITT principle in this circumstance would require the empty clusters to be accounted for in the analysis. Accounting for empty clusters would require strong assumptions to be made about patient characteristics and outcomes based on GP or cluster characteristics.

We therefore plan to present a modified ITT analysis as our primary analysis, where we will analyse clusters, GPs and patients, as they have been randomised, regardless of the intervention they have received, but will not impute missing data. As part of the secondary analyses, we will attempt to examine the potential impact of empty clusters on the intervention effects for the primary outcomes. Reasons for practice and GP withdrawal will be collected, and even in the circumstance of withdrawal, we will seek permission to run the CAT to extract data on patients.

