Our primary analyses of outcomes will include adjustment for the stratification variables (*e*.*g*., geographical location of the practice, number of GPs per practice) and pre-specified potential confounding variables (Figure 3). The potential confounders have been selected through discussion with the investigators and examination of the confounders adjusted for in other similar implementation trials (*e*.*g*., [16,30]). All pre-specified confounders will be included in the models even when no baseline imbalance exists, since confounder selection strategies based on observed data (*e*.*g*., selecting confounders using preliminary statistical tests) result in models with poor statistical properties (*e*.*g*., incorrect type I error rates) [69-72]. If there are outcomes with limited data or events, we will only adjust for the stratification variables and, where appropriate, the baseline of the outcome variable (*e*.*g*., self-report measures, intention, and behavioural constructs). For each outcome, the estimate of intervention effect and its 95% CI will be provided. For primary outcomes, we plan to provide estimates of ICCs and their 95% CI.

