#### Secondary analyses

GEEs fitted to binary outcomes yield unbiased estimates of intervention effect only when data are missing completely at random [73]. As noted previously (in the ‘Analysis subsets’ section), empty clusters arising from practices or GPs withdrawing post randomisation but prior to extraction of patient data may occur, and this may introduce bias. We will attempt to examine the potential impact of empty clusters on the intervention effects for the primary outcomes using weights to allow for patterns of ‘missingness’ [74]. Weights will be created based on proxy measures of clinical behaviour for the key recommendations (*e*.*g*., self-report adherence to cognitive assessment using MMSE, intention to adhere to cognitive assessment using MMSE).

Two inclusion criteria used to define cohort 2 (patients with suspected cognitive impairment) are based on use of the MMSE in the baseline period. If GPs suspect cognitive impairment, patients should receive further assessments using the MMSE, regardless of whether they have been previously assessed. The rate of MMSE assessment is likely to be higher in patients who have received a previous MMSE, since their GP is already more likely to adhere to this recommendation. Consequently, an MMSE assessment in the baseline period may modify the intervention effect for the primary outcome of cognitive assessment using MMSE. We will examine this by fitting a model that includes an interaction term between the intervention group and an administration of the MMSE in the baseline period.

For the primary outcomes, we plan to undertake a per-protocol analysis to estimate the effect of the intervention for the subgroup of GPs who comply with the intervention. Compliance to the intervention is defined as attendance at the workshop.

We plan to undertake explanatory analyses for the primary outcomes to examine if intervention effects are explained by our hypothesized mediators of practitioner behaviour (Figure 2) [75-78]. These explanatory analyses will form a separate publication.

In the IRIS trial, some behaviours will be measured both objectively (through medical records) and subjectively (self-report and behavioural simulation). When objective measures are available, we will examine the predictive validity of the subjective measures; this will aid in interpretation of the subjective measures and contribute evidence of their measurement properties.

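### The no-imputation rule is worded for all missing data, so with the fixed adjustment set it would drop GPs, and possibly practices, whose outcomes were observed but who lack a baseline covariate

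*Protocol article*

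**What the plan says.** All places are in the protocol article, under Effectiveness analyses unless stated.

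- **Analysis subsets, the loss foreseen.** The only loss discussed is that "practices and GPs may withdraw prior to data being extracted on their patients, resulting in empty clusters". Accounting for such clusters is said to need strong assumptions about their patients. Because the record search covers all eligible patients, "bias arising from missing responses and loss to follow-up at the patient level will be minimal".
- **Analysis subsets, the rule.** The modified ITT analysis takes units as randomised, "regardless of the intervention they have received, but will not impute missing data". The clause is not limited to outcomes or to empty clusters. For practices that leave the trial, "even in the circumstance of withdrawal, we will seek permission to run the CAT to extract data on patients".
- **Primary analyses, the covariates.** The models adjust for the stratification variables and the confounders in Figure 3. "All pre-specified confounders will be included in the models even when no baseline imbalance exists". There is one exception: "If there are outcomes with limited data or events, we will only adjust for the stratification variables and, where appropriate, the baseline of the outcome". The examples given there are self-report, intention and behavioural constructs.
- **Secondary analyses.** "We will attempt to examine the potential impact of empty clusters on the intervention effects for the primary outcomes using weights". The weights are built from GP self-report and intention. The section also concedes that the GEE is unbiased only if data are missing completely at random.
- **Data quality assurance.** Returned questionnaires are checked, anomalies are followed up with GPs, and non-responders are phoned.

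**The concern.** A regression model cannot use a record with a blank covariate. If the covariate must stay in the model and may not be filled in, the record is deleted. The argument against imputation is sound for a practice that supplied no patient data. It does not carry over to a practice or GP whose outcome is known and who lacks only a baseline item, yet the rule covers both.

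At stake are the size and the make-up of the analysed sample. Deleting units with observed outcomes departs from analysing everyone as randomised. It also undercuts the effort to extract data from practices that withdraw. The planned weighting does not reach this loss, because it is aimed at practices without extracted data. Its weights come from the same questionnaire, so they may be missing for the same GPs.

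**Working it through.** **1. Which analyses lose records under the stated rules**

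| Covariate | Source | Can it be missing when the outcome is known? |
|---|---|---|
| Location, number of GPs (strata) | Known at randomisation | No |
| Patient age, sex, baseline behaviours | Record search (Identification of patients; Table 2) | Essentially no, as they come with the outcomes |
| Baseline self-report, intention, constructs, as adjustment for the same score at nine months | GP questionnaire (Table 2) | Yes |
| GP- or practice-level confounders in Figure 3, if any | Not shown; items of this kind in Table 5 could not come from the record search | Yes, if any are in the model |

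The third row does not depend on Figure 3: even the reduced adjustment set keeps the baseline of the outcome. It applies to self-report, intention and constructs. The clinical vignettes have no baseline measurement in Table 2, so they are not affected in this way.

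The fourth row is conditional. Descriptive analyses at baseline speaks of potential confounders at patient, GP and practice level, and Table 5 lists many, but it does not say which enter the models. If one does, a missing practice-level value removes the whole practice. A missing GP-level value removes that GP's patients. This will often be the whole practice, because Primary analyses expects few practices with more than one GP.

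**2. The plan's own sample size**

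Inputs (Sample size): 50% versus 65%, 20 patients per practice, CV 0.7, ICC 0.10, two-sided 5%, power 90%, 25% attrition.

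- Individually randomised n per arm, with mean proportion 0.575: [1.960 × √(2 × 0.575 × 0.425) + 1.282 × √(0.50 × 0.50 + 0.65 × 0.35)]² / 0.15² = 226.2, so 227.
- Design effect: 1 + [(0.7² + 1) × 20 − 1] × 0.10 = 3.88.
- Practices per group: 227 × 3.88 / 20 = 44.04, so 45.
- With attrition: 45 / 0.75 = 60.

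Both stated figures, 45 and 60, are reproduced.

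**3. Power if more practices are lost**

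For k analysed practices per group, effective n = 20k / 3.88, and power = Φ{[0.15 × √n − 1.960 × √0.48875] / √0.4775}. Here 0.48875 = 2 × 0.575 × 0.425 and 0.4775 = 0.25 + 0.2275.

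The further loss is an assumption, applied to the 45 practices left after the full 25% allowance is used.

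| Further loss | Practices per group | Effective n | Power |
|---|---|---|---|
| 0% | 45 | 232.0 | 90.7% |
| 10% | 40.5 | 208.8 | 87.6% |
| 15% | 38.25 | 197.2 | 85.7% |
| 20% | 36 | 185.6 | 83.5% |

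If withdrawal and covariate loss together take no more than 15 of the 60 practices per group (25%), at least 45 remain and power is not below the 90.7% in the first row.

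**The case against.** **The clause may be meant more narrowly.** It concludes an argument about empty clusters, complete-case deletion is never stated, and the handling of a missing covariate is often left to a statistical analysis plan. The context does suggest that empty clusters were in mind. As worded, however, the rule covers all missing data, and a later plan that filled in covariates by their mean would contradict it. A missing category for categorical variables arguably would not.

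**Figure 3 is not shown.** A reader might infer that whole practices will be discarded from the primary analysis. The article does not establish this: Table 5 is descriptive, and the model covariates may all come from the record search or the stratification. This objection stands for the primary outcomes. It does not touch the GP-level outcomes.

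**Selection towards engaged GPs.** A reader might also infer that practices which disengage or withdraw are the ones lost, so that the analysed set tilts towards engaged GPs. The support is weak. The introduction to Methods and the section on timing both say that baseline questionnaires have been collected, and later withdrawal does not erase answers already held. The follow-up of missing items and non-responders should also keep gaps few.

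**The 25% allowance.** Its causes are not stated in the article, so it may absorb some or all of this loss. That stands for power. It does not justify deleting units whose outcomes are known.

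**The reduced adjustment set.** It is triggered by sparse data or events for an outcome, and is not clearly meant for a missing covariate. For questionnaire outcomes it keeps the very baseline value at issue.

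**Conclusion.** The point holds in a limited form and is worth correcting. The rule against imputation is broader than its justification. With the adjustment rule, it would remove from the linear mixed models any GP with a nine-month score but no baseline score. This follows from the text whatever Figure 3 contains.

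For the two primary outcomes the loss is conditional on Figure 3 including a questionnaire-derived GP or practice covariate, and on that covariate being missing in some practices with extracted outcomes. The size is unknown. Power falls below 90% only if the total loss goes far enough beyond the 25% allowance. On assumed further losses of 10% to 20% it would be about 88% to 84%, a moderate reduction. The sample size calculation itself is correct on its inputs. The article does not support a claim that the primary comparison is biased or that its power will fall short.

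**What to change.** In Analysis subsets, limit the rule to outcomes and add a rule for covariates, for example: *Missing outcomes will not be imputed. Missing baseline covariates, including baseline values of GP-level outcomes, will be filled by a simple method that ignores arm and outcome (the overall mean for continuous variables, a missing category for categorical ones), so that every practice and GP with an observed outcome is analysed.*

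This needs no new data, only the added wording and a few lines of code. The introduction to Methods says that collection of patient-level data had only just begun, so the rule could be settled before outcomes are analysed. The method suits a randomised comparison as long as the covariates are true baseline values, recorded before allocation could influence them. The downside is slightly weaker covariate adjustment for the affected practices and GPs. The weighting analysis for empty clusters can stay as it is.
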